**Reviews**								
3 Month	✔	✔	✔	✔	✔			
6 Month	✔	✔	✔	✔	✔			✔
9 Month	✔	✔	✔	✔	✔			
12 Month	✔	✔	✔	✔	✔			✔
15 Month	✔	✔	✔	✔	✔			
18 Month	✔	✔	✔	✔	✔	✔	✔	✔
**Follow-up:**								
6mFU	✔	✔	✔	✔	✔	✔	✔	✔
12mFU	✔	✔	✔	✔	✔	✔	✔	✔
24mFU	✔	✔	✔	✔	✔	✔	✔	✔

### The analysis of data

To preserve neutrality, no data will be analysed until all subjects have reached the six month follow-up point. An intention-to-treat analysis will be performed in the first instance (i.e. analysing all available data from randomised participants) using for all analyses the STATA, version 11.0 package. The numbers and percentages of losses to follow-up at 12, 18, and 24 months after randomisation will be reported and will be compared between the treatment arms with absolute risk differences (95% CIs). Any deaths and their causes will be separately reported. To increase the power and precision of the estimated treatment effect, missing baseline covariates will be imputed for our main analysis using either mean or regression imputation [77]. All available results will be used without missing outcomes being imputed. Primary analyses will be based on the assumption of ignorable drop-outs. In secondary analyses, missing values will be replaced by multiple imputations using Markoff Chain Monte Carlo methods [78].

For continuous outcome variables, the differences in mean score between those randomised to either arm of the trial will be examined using analysis of covariance adjusting by 1) baseline value of outcome 2) baseline value of the outcome, gender and age. The assumption of linearity will be assessed by residual analysis; if necessary, bootstrapping techniques will be employed. Sensitivity analyses will be conducted to take into account missing data using multiple imputation, which assumes data are 'missing at random'. For continuous response variables, statistical analyses will be based on linear mixed models [79].

For binary responses, mixed-model logistic regression models and generalized estimating equations will be used [80]. Logistic regression will be used to compare proportions of patients that have lost their diagnosis during the treatment and follow-up period in the two groups using an HRSD of 14 as criterion. Analysis of 'time to first recovery' and ‘time to first relapse’ outcome will also be conducted using survival analysis methods and the log-rank test for bivariate comparisons and Cox's proportional hazards to adjust for gender, stratification variables and time spent on treatment prior to randomisation. The dependencies between design points in the case of linear mixed models will be accounted for by assuming an unstructured correlation structure.

Statistical significance will be tested with the Wald test, and CIs will be established by the Delta method [81]. Time will be handled as a categorical variable with five possible values - 0, 6, 12, 18, 24 months. The basic model will include the main effects of time, of treatment group, of the difference between theoretical and realised date of measurement and first order interaction of time and treatment. A complete model will include potential confounding factors (e.g. age group, gender etc). Complementary analyses will be carried out adjusting for the baseline level of outcome measures. 'As treated' models will be carried out by including variables describing compliance (e.g. waiting time from randomisation to initiation, degree of participation, including an indicator whether the patient received the study treatment) and auxiliary treatments such as medication.

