## Design & methods

### The hypotheses

As detailed below, the primary hypothesis is that PPD is superior in effectiveness to a comunity treatment as usual control group (TAU) using the Hamilton Depression Rating Scale as its primary outcome measure. The study tests the effectiveness of psychoanalytic therapy with a research sample of patients suffering from TRD, as an exacting test of its hypothesised ability, both to reduce symptoms over the immediate term, and to yield significant reductions in long-term susceptibility to depression. The trial has been designed to test the effectiveness of the PPD model as it might be offered in the context of an ordinary psychotherapy clinic, to patients with long term mental health problems including major depression. The aim therefore was to stay as close as possible to the setting in which those patients with chronic TRD may be referred, and to offer the therapy in a form as little modified as possible, while meeting what is required by trial methodology. A pilot study of two cases was conducted before commencing the study proper, to obtain information about the practicalities of both the therapeutic and the research enterprises.

We employ an intention-to-treat methodology with all eligible, consenting participants. The participants are randomised into two groups: one receives a target of 60 sessions of once-weekly psychoanalytic psychotherapy for depression (PPD) over a period of eighteen months [in practice the actual number is allowed to vary slightly according to factors such as the timing of holidays], while the other represents a ‘treatment as usual’ (TAU) control condition. The PPD group is assessed over the trial intervention and for a two year follow-up. The TAU control group is observed over the same 3.5 year period.

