#### *Sample size, power calculation & primary outcome*

Because the analysis of the expected primary outcome is concerned with testing superiority of PPD relative to a comunity treatment control group (TAU), we employ an 80% one-sided confidence interval (CI) to assess potential non-inferiority. The trial is powered to detect a 35% difference in effectiveness between PPD and TAU on the Hamilton Depression Rating Scale HRSD-17 [44] with alpha at 0.05 and beta at 0.9. The primary outcome for treatment efficacy is the rating of depressive symptoms by an objective assessor blind to treatment allocation. Estimating effect-size on the basis of previous trials summarized in meta-analyses using the HDRS-17 in psychosocial treatments, with or without pharmacological therapies (e.g. [45]), we could achieve the target levels of alpha and beta with 80 cases randomised equally into two arms. However, this does not take into account within-therapist correlations. Based on statistical analysis of data from another trial of long term psychodynamic therapy with a similarly heterogeneous population [46] we have conservatively assumed an intra-cluster correlation coefficient for therapists of 0.05. With a minimum of 10 therapists delivering each therapy, each seeing on average 5 subjects, the study will have 80% power to reject inferiority with a non-infidelity margin equal to an effect size of 0.5 using an 80% one-sided confidence interval, on the basis of a 90% follow-up rate to 6 months. Given the pragmatic focus of the trial, the degree of adherence to treatment protocols is of considerable interest. The main analyses will be based on an intention-to-treat and complementary “as treated” bases.

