### The limitations of the trial

When compared with other long-term psychoanalytic psychotherapy (LTPP) outcome studies our N of 129 may be regarded as large, but considered statistically the trial is somewhat under-powered. Unfortunately, the very large and expensive treatment service resources necessary for a significantly bigger sample are simply not available. A second limitation is to be found in the impossibility of concealing treatment allocation from research interviewers. We seek to mitigate this by double-rating the primary outcome measure using independent raters working with anonymised recordings. Another limitation is the inherent variability both of our test treatment and of the TAU comparison condition. Although our design includes a treatment manual, assessment of adherence, and careful recording of the TAU care control patients actually receive this still does not permit the kind of quasi-experimental assessment of the impact of the components that are possible with less complex treatment procedures. Finally, in a long-term trial with patients of this kind the inevitably high rate of attrition could easily cause a statistically unacceptable standard mean error [119].

In this discussion we have considered only some of the issues in long-term randomised trials of complex treatments for complex mental health conditions. We opted for this composite, ecological design as a first stage study in which a standard RCT was complemented by evaluative methods in order to produce in-depth models helpful in understanding the condition itself, as well as with the development of more optimal treatment and case management. We want to emphasise the importance of research procedures capable of meeting the challenges posed by the disorder. Some knowledge of the complex nature of the disorder is also necessary to properly evaluate both the structure of the research, and its eventual findings.

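### The period-wide lost-diagnosis proportion, compared by logistic regression on available visits, depends on how long each patient is followed, so any difference in drop-out between arms would appear as a treatment difference

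*Protocol article*

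**What the plan says.** All references are to the protocol article.

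- **Endpoint and model.** The analysis of data: "Logistic regression will be used to compare proportions of patients that have lost their diagnosis during the treatment and follow-up period". The comparison is between the arms, and the threshold is a Hamilton score of 14. This reads as one yes/no per patient over the whole period.
- **Period.** The hypotheses section sets 18 months of therapy and two years of follow-up for PPD; for the control arm, "The TAU control group is observed over the same 3.5 year period". Table 2 schedules the HRSD at nine post-baseline visits: months 3, 6, 9, 12, 15 and 18, then 6, 12 and 24 months into follow-up (months 24, 30 and 42).
- **Missing outcomes in the main analysis.** "All available results will be used without missing outcomes being imputed", and "Primary analyses will be based on the assumption of ignorable drop-outs".
- **Other planned analyses.** The same section has multiple imputation as a secondary analysis, mixed logistic models and GEE for binary responses, and log-rank and Cox analyses of time to first recovery. It also compares losses between arms at 12, 18 and 24 months.
- **Drop-out.** The sample size section works "on the basis of a 90% follow-up rate to 6 months". The limitations section refers to "the inevitably high rate of attrition". The Randomisation section of the Discussion says that some patients may leave because they did not get the allocation they wanted, and others because they fear what treatment involves.

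**The concern.** A yes/no over 42 months is settled early for a patient who meets the criterion at an attended visit. It is not settled for a patient who leaves before meeting it. With nothing imputed and all available results used, a patient who leaves after month 9 without a qualifying score would be counted as a no after three opportunities, while a completer has nine. Logistic regression on one row per patient has no censoring, so it treats the two as equivalent.

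The proportion therefore mixes recovery with length of observation. If one arm is followed for longer, it collects more recoveries even if the two treatments are identical. The ignorable drop-out assumption protects a likelihood model of the repeated scores. It does not protect an indicator built from whichever visits were attended: the distortion is there even when drop-out is completely at random. The HRSD is the primary measure and the categorical analysis at 14 is one of its two stated uses, so this comparison will be read closely.

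**Working it through.** **The plan's own figure.** The article gives no expected value for this proportion and no drop-out beyond 6 months. The only figure near it is the 80 patients for a 35% difference at alpha 0.05 and 90% power (the stated beta of 0.9, read as power). Assume a two-sided test and a control rate of 25% (not in the document), so 25% v 60%, mean 42.5%:

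n per arm = [1.96·√(2·0.425·0.575) + 1.2816·√(0.25·0.75 + 0.60·0.40)]² / 0.35² = (1.370 + 0.838)² / 0.1225 = 39.8, so 40 per arm and 80 in all.

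Control rates of 20% to 32.5% give 78 to 82. This fixes the scale (35 percentage points) and has no other bearing on the point.

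**Inputs**
- Visits t₁…t₉ = 3, 6, 9, 12, 15, 18, 24, 30, 42 months (Table 2).
- 129 randomised (limitations section), 67 in PPD (typology section), so 62 in TAU.
- Assumed: the same chance p of meeting the criterion at each visit in both arms (no treatment effect), and random drop-out at a constant rate reaching d by month 42.

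**Formula.** The chance of attending visit k is (1−d)^(t_k/42). With independent visits:

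P(scored yes, all randomised) = Σ p(1−p)^(k−1)·(1−d)^(t_k/42).

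Among patients with at least one visit, divide by (1−d)^(3/42).

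**Example, p = 0.10.** With full follow-up both arms have 1 − 0.9⁹ = 61.3%. With d = 20% the sum is 56.7%; divided by 0.984 it is 57.7%. With d = 40% it is 51.7%; divided by 0.964 it is 53.6%. The spurious difference is 4.1 points among patients with a visit and 5.1 points among all randomised (from unrounded values).

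**Range over p = 0.05 to 0.30**

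| Drop-out by month 42 | At least one visit | All randomised |
|---|---|---|
| 20% v 40% | 2.7 to 4.5 points | 3.3 to 6.0 points |
| 10% v 40% | 4.0 to 6.5 points | 4.9 to 8.7 points |
| 30% v 30% | 0 | 0 |

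At 30% v 30% and p = 0.10 both arms read 55.7% instead of 61.3%: no arm difference, but both rates are too low.

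**Against sampling error.** SE = √(0.577·0.423/67 + 0.536·0.464/62) = 0.087, so 4.1 points is about 0.5 SE.

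**Type I error** (4,000 simulated null trials, 67 v 62, two-sided 5% test, patients with at least one visit). Independent visits: 8.2% at 20% v 40%, 10.6% at 10% v 40%. With a patient random intercept (logit SD 1.5 or 2) the spurious difference shrinks to 2.2 to 4.2 points and the error rate to 5.6% to 8.0%. Full follow-up data in the same runs gave 4.6% to 6.1%, so the low end is barely distinguishable from nominal.

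**Drop-out that depends on the last observed score.** No treatment effect; one arm loses 8% per interval after a non-remitted score and 2% after a remitted one, the other arm 3% throughout. Scoring on attended visits gives a spurious 5 to 6 points among patients with a visit. Restricting to completers gives 3.4 to 4.5 points in the opposite direction. Kaplan-Meier with leavers censored recovers the true proportion in both arms.

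**The case against.** **The scoring rule is inferred.** The article does not say that the yes/no is taken over attended visits, nor how leavers are classified. The sentence follows one on mixed logistic models and GEE, and the section treats time as categorical, so a comparison at each time point is a tenable reading. Under it the fewer-visits mechanism does not arise: month-42 status alone, or completers alone, gave no difference and about 5% rejection under random drop-out. This stands as a limit on certainty. But the wording names a period, not a visit, and the all-available-results rule argues against completers only, which is itself biased when leaving depends on the last score.

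**Remedies are already planned.** Time to first recovery censors leavers, and multiple imputation is in the secondary analyses. This stands and limits the harm. It does not repair the logistic comparison, which remains a named analysis.

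**It is detail for the analysis plan.** Only in part. The article itself fixes the period-wide endpoint, the model and the no-imputation rule, and the difficulty lies in combining them.

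**Stronger readings that a reader might infer and that the document does not support**
- *No leaver can be scored.* A leaver who met the criterion at an attended visit is already a yes. Only leavers who had not met it are undetermined.
- *Unequal loss is to be expected, and it will favour PPD.* The Discussion gives reasons for leaving that work in both directions: disappointment with the allocation, and fear of the treatment. The limitations section expects high attrition but does not say it differs by arm.
- *The 90% at 6 months fixes the drop-out rates.* Constant loss per visit gives 0.95² = 0.90 at month 6 and 0.95⁹ = 0.63 at month 42. Constant loss per month gives 0.90⁷ = 0.48. The figure is not given by arm, so it cannot set an imbalance.

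**Conclusion.** The point holds in limited form. On the natural reading, the available-visit logistic regression makes the lost-diagnosis proportion depend on length of follow-up, and unequal drop-out alone would then produce an arm difference. Assuming ignorable drop-out is no protection.

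The size is modest: about 3 to 9 points for drop-out imbalances of 20 to 30 points by month 42, with type I error of about 6% to 11%, against a design difference of 35%. The upper ends assume independent visits; within-patient correlation brings the difference to about 2 to 4 points. Every by-arm drop-out rate, per-visit probability and correlation here is assumed. Neither the presence of an imbalance nor its direction is established. The plan should be changed because a better analysis is already in it, not because a large bias has been shown.

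**What to change.** Replace the available-visit logistic regression as the main version of this comparison with one of the following, and say which:

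1. Estimate the cumulative proportion who lost the diagnosis at 18 and 42 months in each arm from the planned time-to-first-recovery analysis (Kaplan-Meier or discrete-time, since status is known only at visits), with leavers censored at their last visit. State that first recovery uses the same HRSD criterion.
2. Multiply impute the missing visit scores, derive the yes/no in each completed data set, then compare and pool.

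If the logistic regression is kept as a supporting analysis, state how patients with incomplete follow-up who have not met the criterion are classified. Extending the between-arm comparison of losses from 24 to 30 and 42 months would show whether an imbalance exists.

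The cost is wording only, since both methods are already planned; intervals will be slightly wider. Censoring still assumes that, among patients not yet recovered, leaving is unrelated to later recovery. Imputation needs a comparable assumption.

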### Randomisation

TRD participants vary in their resilience to the significant stresses that research involves. One of the most potent stresses is randomisation powerfully stirs up feelings of rejection especially in those who already have histories of severe loss or abandonment. Subjects who had strong wishes for the PPD treatment feel disappointed, hurt or angry when the allocation is not that for which they hoped. These subjects may then drop-out. Others drop out because of their fears about what treatment may involve. When participants are told of their treatment allocation, it is important that the research staff show sensitivity to the situation. The psychoanalytically-trained research clinicians allow space in the initial clinical interview for the subject to express how they felt about the allocation they received. As well, the research clinician has to be mindful of the underlying feelings aroused by the long research process especially with those who were randomised to the TAU control.

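### Un-imputed ANCOVA and a linear mixed model are listed unranked for the same outcomes, but only the mixed model fits the plan's ignorable drop-out assumption

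*Protocol article*

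**What the plan says.** All of this is in the Protocol article, The analysis of data, unless stated otherwise.

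- Missing outcomes, and the assumption made about them: "All available results will be used without missing outcomes being imputed. Primary analyses will be based on the assumption of ignorable drop-outs". Multiple imputation is kept for secondary and sensitivity analyses.
- Continuous outcomes, first method: "analysis of covariance adjusting by 1) baseline value of outcome 2) baseline value of the outcome, gender and age".
- Continuous outcomes, second method: "For continuous response variables, statistical analyses will be based on linear mixed models", with an unstructured correlation. The basic model has time, treatment and their interaction, with time at 0, 6, 12, 18 and 24 months.
- Binary outcomes: mixed-model logistic regression and GEE. In addition, "Logistic regression will be used to compare proportions of patients that have lost their diagnosis", with HRSD 14 as the criterion, over the treatment and follow-up period.
- Table 2 schedules the HRSD at baseline, every 3 months to month 18, and at 6, 12 and 24 months of follow-up.
- Discussion, The limitations of the trial, expects high attrition but gives no figure. Discussion, Randomisation, describes patients disappointed by their allocation: "These subjects may then drop-out. Others drop out because of their fears about what treatment may involve".

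**The concern.** Drop-out that depends on earlier observed scores is ignorable only for an analysis that uses those scores. The linear mixed model does so through its covariance. An ANCOVA at one visit, with no outcome imputation, conditions only on arm, baseline and perhaps gender and age. It therefore needs a narrower condition than the one the plan states: missingness must be unrelated to the outcome once those few variables are known.

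A patient who leaves after month 15 has five post-baseline HRSD scores (months 3, 6, 9, 12 and 15). None of them enters an ANCOVA at month 18 or 24. The two listed methods can then disagree on the same data only because of who was excluded, and nothing in the article says which result is the trial's answer. The available-case result describes patients still attending, whereas the stated aim is an intention-to-treat comparison.

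**Working it through.** The plan gives no figure for missing-data bias, so there is none to reproduce. The check is in principle first, then by simulation.

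**Principle.** Let Y0 to Y24 be the HRSD at each visit and R = 1 if Y24 is observed.

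- Ignorable drop-out lets R depend on arm and on all scores observed before leaving.
- Available-case ANCOVA needs E[Y24 | R = 1, arm, Y0] = E[Y24 | arm, Y0]. This fails when R depends on, say, Y18, because Y18 predicts Y24 beyond Y0.
- ANCOVA bias = (shift among those observed in PPD) - (shift among those observed in TAU). Equal shifts cancel. Different dependence, or the same dependence at different rates, leaves a remainder.

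**Inputs from the article.** Arms of 67 (PPD; psychoanalytic typology section) and 129 - 67 = 62 (TAU; 129 from The limitations of the trial). The visits are the five in the basic model, and remission is HRSD of 14 or below. Follow-up is given only as 90% to 6 months (Sample size section).

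**Assumed, because the article does not give them.** HRSD SD 6; correlation between visits 0.5 or 0.7; monotone drop-out from month 12 with logit = intercept + b x (last HRSD - 17)/6, where b is 0, +0.8 or -0.8. There were 200,000 patients per arm for bias and 4,000 trials of 67 v 62 for type I error. The true effect was zero or 3 points (0.5 x SD 6; 0.5 is the article's margin, not an expected effect).

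**Results at month 24, absolute bias.**

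| Drop-out pattern | Missing | ANCOVA bias (points) | Remission difference bias (percentage points) |
|---|---|---|---|
| Unrelated to scores | about 37% | about 0 | about 0 |
| Same dependence and rate in both arms, no effect | 40-41% | 0.01-0.02 | 0.1 |
| Same drop-out model in both arms, 3-point effect | 33-41% | 0.10-0.12 | about 1 |
| Dependence in one arm only | 33-41% | 0.35-0.55 | 5.5-9 |
| Opposite dependence by arm | 33-41% | 0.84-1.11 | 12-18 |
| Same dependence, unequal rates | 27% v 56-57% | 0.35-0.46 | 6-8 |
| One-arm or opposite dependence, few losses | 8-11% | 0.09-0.25 | 2-5 |

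A likelihood fit with unstructured covariance stayed within 0.03 points of the truth throughout. With no true effect and N = 129, ANCOVA type I error was 5.0-5.2% when drop-out was unrelated to scores, 6.9-7.6% with one-arm dependence, and about 14% with opposite dependence.

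**Second set of assumptions.** Carrying the 90% on for four half-years leaves 0.9^4 = 66% observed. With odds of leaving doubled per SD worse score in TAU and no dependence in PPD, ANCOVA gave 2.59 instead of 3.01 points: (2.59 - 3.01)/3.01 = -14%. Opposite dependence gave -29% or +28%, and equal dependence under 1%. At 95% retention per half-year the one-arm bias fell to -7%. For GEE on the log-odds scale, independence working correlation was biased by about -4% to -13%, exchangeable by about -1% to +3%.

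**Visits used.** The five time points omit months 3, 9 and 15. For the patient leaving after month 15, the mixed model as specified sees two of the five post-baseline scores (months 6 and 12), so drop-out driven by the month-15 score would be only partly captured there too.

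**The case against.** A reader might infer that ANCOVA and logistic regression are the trial's main analyses and that they discard everyone who misses a visit. The article does not support that.

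- It never calls either method main or primary. It speaks of a main analysis only when imputing baseline covariates. The sentences on available results and ignorable drop-out fit a likelihood mixed model well, and the article specifies that model in most detail. It also calls further analyses adjusting for baseline complementary. Taking the mixed model as the lead is a fair reading.
- For binary outcomes it lists mixed-model logistic regression, which also keeps each patient's observed visits.
- The plain logistic endpoint is loss of diagnosis over the whole period. Nothing says that an early leaver with scores on file is excluded. The remission biases above apply only to a visit-level comparison.
- Imputation under missing at random is already planned, once in the ANCOVA paragraph itself.

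A second tempting inference is that the Discussion shows the bias will occur. It gives allocation-related reasons for leaving (disappointment, fear of treatment), not dependence on interim scores. Patients who leave on learning their allocation may have no interim scores to use.

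These objections remove the stronger reading and lower the weight of the point. They do not rank the two methods, and they do not make an un-imputed ANCOVA valid under the assumption that the plan states.

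**Conclusion.** The point holds in a limited form. Two methods are listed for the same continuous outcomes with no stated precedence. Only the likelihood mixed models match the ignorable drop-out assumption when drop-out follows earlier scores; for the logistic one, this is so as far as the binary history it models explains the drop-out. Available-case ANCOVA, and visit-level remission by plain logistic regression or independence GEE, can be biased in either direction.

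The size is conditional. At about a third or more missing, it is roughly 0.4-0.6 HRSD points with one-arm dependence and 0.8-1.1 with opposite dependence. Against an assumed 3-point effect, the runs that included that effect gave 0.35-0.41 points (12-14%) and 0.84-0.95 points (28-32%). It is near nil when dependence and rates are equal, and small when few are lost. These figures rest on the assumed SD, correlations and drop-out models. This is a moderate point about precedence and labelling, and it is separate from drop-out that is not at random.

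**What to change.** In The analysis of data:

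1. Name the likelihood-based linear mixed model as the primary continuous analysis and the mixed-model logistic regression as the lead repeated binary analysis.
2. Include all scheduled HRSD visits, adding months 3, 9 and 15 to the five time points.
3. Run any ANCOVA, GEE or visit-level logistic comparison on data multiply imputed by arm from baseline and interim HRSD and BDI-II scores, with remission derived from the imputed HRSD.
4. Label un-imputed ANCOVA and logistic results as supportive.

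The cost is wording and modest programming: the methods are already planned and the scores already collected. There are two downsides. Results lean on the imputation model. The unstructured covariance also grows from 5 x 6/2 = 15 parameters to 8 x 9/2 = 36 at N = 129 (10 x 11/2 = 55 if the 12- and 24-month follow-up visits are modelled too), so a fallback structure should be named in case the fit fails.

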### Randomisation

The secure, automated telephone randomisation was provided by the Clinical Trials Unit at University College London. Minimisation is necessary to limit the impact of factors that might moderate treatment response. A gender bias has been identified in unipolar depression: UK prevalence is estimated at 28 per 1000 in women compared to 24 per 1000 in men [47]; pre-treatment severity has been shown to affect treatment outcome [48]; and antidepressant medications are the most frequent treatment for depression. Therefore, a computer-generated, adaptive minimisation algorithm incorporating a random element was employed to control for gender, depression severity (BDI-II of 21–39 or of 40+) and medication (on/off). Only the information needed for the minimisation algorithm was provided to the Clinical Trials Unit.

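### The stated HRSD models do not carry through the minimisation factors, and the primary model, on which the handling of baseline HRSD depends, is not named

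*Protocol article*

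**What the plan says.** Under Randomisation, the protocol article says that an "adaptive minimisation algorithm incorporating a random element was employed to control for gender, depression severity" in two BDI-II bands (21 to 39, and 40 or more) and medication (on or off). The reason it gives is: "Minimisation is necessary to limit the impact of factors that might moderate treatment response". For severity it adds that "pre-treatment severity has been shown to affect treatment outcome".

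Under The analysis of data, it describes several models:

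- Arm differences in continuous outcomes are examined by "analysis of covariance adjusting by 1) baseline value of outcome 2) baseline value of the outcome, gender and age".
- "For continuous response variables, statistical analyses will be based on linear mixed models". Time has five categories, 0 to 24 months in six-month steps, and the correlation is unstructured. The basic model contains time, arm, deviation from the scheduled visit date, and time by arm. The complete model adds confounders from an open list that gives age group and gender as examples.
- "Complementary analyses will be carried out adjusting for the baseline level of outcome measures".
- The survival outcomes use "Cox's proportional hazards to adjust for gender, stratification variables and time spent on treatment prior to randomisation".
- Medication is otherwise named only in the as-treated models, as an auxiliary treatment.

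The article does not say whether the ANCOVA or the mixed model is the primary HRSD analysis.

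**The concern.** Minimisation makes the arms alike on the chosen factors. If those factors predict outcome, the treatment estimate varies less from trial to trial than it would under simple randomisation. A model that omits them leaves their variation in the residual, so the reported standard error does not show the precision that the design has bought. The article accepts the principle for its Cox models but does not apply it by name to HRSD, the primary outcome.

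The mixed model raises a second matter. Month 0 is one of the response times and arm has a main effect, so the arm means at baseline are free to differ. Randomisation makes the expected baseline difference zero. Estimating it anyway spends information.

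What is at stake in both cases is precision. The article itself calls its sample of 129 somewhat under-powered (The limitations of the trial).

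**Working it through.** **1. Which model names which factor**

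| Model | Gender | BDI-II severity | Medication at randomisation | Baseline HRSD |
|---|---|---|---|---|
| ANCOVA 1 | no | no | no | covariate |
| ANCOVA 2 (also age) | yes | no | no | covariate |
| Basic mixed model | no | no | no | month-0 response, arm effect free |
| Complete mixed model | example in open list | not named | not named | month-0 response |
| Complementary analyses | not stated | not stated | not stated | covariate |
| Cox | yes | through stratification variables | through stratification variables | not stated |

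This reads stratification variables as the minimisation factors; the article names no others.

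**2. The plan's own figure**

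The sample-size section gives 80 participants for a 35% difference at alpha 0.05, with its beta of 0.9 read as 90% power. Two proportions of 0.25 and 0.60 (base rate assumed), two-sided, without continuity correction, give 40 per arm, so 80 reproduces. No baseline correlation or R² enters that calculation, so it neither supports nor weakens the present point.

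**3. Cost of omitting the minimisation factors**

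Let R² be the joint partial R² of the omitted factors beyond baseline HRSD (assumed; none is given). The ratio of model-based standard errors, omitted to included, is 1/√(1 − R²). With the factors balanced, the true two-sided size of a nominal 0.05 test is 2[1 − Φ(1.96/√(1 − R²))].

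| R² | SE ratio | True size |
|---|---|---|
| 0 | 1.000 | 0.050 |
| 0.02 | 1/√0.98 = 1.010 | 0.048 |
| 0.05 | 1/√0.95 = 1.026 | 0.044 |
| 0.10 | 1/√0.90 = 1.054 | 0.039 |

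Adding two terms to ANCOVA 2 takes the residual degrees of freedom from 129 − 5 = 124 to 122. Multiplying each ratio by √(122/124) gives 0.992, 1.002, 1.018 and 1.046. At R² of 0.02 or less there is next to nothing to gain.

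**4. Cost of the free month-0 arm effect**

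Inputs: 67 in the PPD arm (section on the typology of chronic depression) and 129 − 67 = 62 in TAU. The correlation ρ between baseline and follow-up HRSD is assumed, with equal standard deviations at both times. In outcome SD units, k = √(1/67 + 1/62) = 0.1762, and the standard errors are:

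- baseline-adjusted: k√(1 − ρ²)
- change contrast (arm by time): k√(2(1 − ρ))
- plain arm difference at one visit: k

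| ρ | Adjusted | Change | Visit difference | Change/adjusted | Visit/adjusted |
|---|---|---|---|---|---|
| 0.3 | 0.1681 | 0.2085 | 0.1762 | 1.24 | 1.05 |
| 0.5 | 0.1526 | 0.1762 | 0.1762 | 1.155 | 1.155 |
| 0.7 | 0.1258 | 0.1365 | 0.1762 | 1.085 | 1.40 |

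An exact generalised least squares calculation for five time points with equal correlations reproduces these ratios when the adjusted analysis is a mixed model with a common baseline mean. With dropout rising to 20% at the last visit, the change/adjusted ratios become 1.20, 1.13 and 1.07.

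As an illustration, take a standardised effect of 0.5 (assumed), a two-sided 0.05 test, and no clustering or dropout. Power at ρ of 0.3, 0.5 and 0.7 is 0.845, 0.906 and 0.978 adjusted, against 0.669, 0.810 and 0.956 for the change contrast.

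**5. Sensitivity to equal SDs**

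If r is the baseline SD divided by the follow-up SD, the variance ratio of change to adjusted is (1 + r² − 2ρr)/(1 − ρ²) = 1 + (r − ρ)²/(1 − ρ²). Entry thresholds could make r less than 1. The change-contrast loss then shrinks as r falls towards ρ and vanishes at r = ρ. The adjusted analysis is never worse.

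**The case against.** The strongest reply is that both ANCOVAs already contain baseline HRSD. A reader might infer that the main HRSD analysis ignores baseline, or that omitting BDI-II band and medication is what costs the 8% to 24% shown for the change contrast. The article supports neither inference. The larger ratios concern only the basic mixed model, and only if that model is the main test. The same section says that missing baseline covariates are imputed for the main analysis to gain power and precision, which points, if anything, towards a covariate-adjusted main analysis. Nor does the mixed model discard baseline: month 0 is in it as a response. This part of the reply stands and limits the point.

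Two further replies stand in part. Baseline HRSD already carries some of the severity information, so the extra yield from BDI-II band may be small. For medication, the article says only that antidepressants are the most frequent treatment; it cites an effect on outcome for severity alone.

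A last reply is that covariate lists are commonly left to the analysis plan, and the complete model's list is open-ended. That is fair for the logistic and GEE models, whose covariates are simply not listed here. It does not answer the ANCOVAs and the basic mixed model, whose terms are written out and differ from the article's own allocation scheme and Cox model.

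**Conclusion.** The point holds as an inconsistency with a modest cost in precision. The listed HRSD models leave out factors on which allocation was minimised, while the Cox model includes them. The consequence is a model-based standard error that is somewhat too large. The excess is about 1% to 5% for an assumed partial R² of 0.02 to 0.10, nil at 0, and not determinable from the documents.

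The baseline matter is conditional. If the basic mixed model is the main HRSD test, its change contrast has a standard error about 1.24, 1.155 or 1.085 times the baseline-adjusted one at assumed ρ of 0.3, 0.5 or 0.7 with equal SDs. If the ANCOVA is main, there is no such loss.

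A reader might also infer bias or an excess of false positives. Neither follows: the omission leaves the estimate valid and makes the test conservative.

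**What to change.** Name one primary HRSD model. Include baseline HRSD as a covariate, or constrain the arm means to be equal at month 0. Add gender, BDI-II severity and medication at randomisation. Enter BDI-II as continuous, or as below 40 against 40 and above. Entry is possible on an HRSD of 14 with BDI-II below 21 (Recruitment & the determination of eligibility), and the 21 to 39 band has no place for such participants.

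Use the same factors in the logistic and GEE models, as the Cox model already does, and keep the unadjusted model as supportive.

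The cost is wording in the analysis plan. Baseline HRSD and BDI-II are collected (Table 2), and gender and medication were supplied for the minimisation. The choice should be fixed before any outcome data are analysed by arm.
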